#### **6.2.2 Secondary Endpoint Events**

Information on secondary safety and immunogenicity endpoints will be collected according to the following criteria:

- (1) All Grade 1 and 2 adverse events occurring within 4 weeks after each vaccination;
- (2) The following responses will be measured at 2, 4, 8, 12, 16, 20, and 24 weeks after

the last vaccination:

- Titers of HIV total antibodies, Env, Gag binding antibodies, and HIV neutralizing antibodies;
- Proportions of HIV-specific cytokines such as IFN- $\gamma$  and IL-2;
- Binding antibody titers against vaccinia virus following rTV immunization.

### 6.3 Recruitment of Study Subjects

Healthy volunteers will be recruited by the National Center for AIDS/STD Control and Prevention (NCAIDS) through outreach at universities and community organizations. Detailed information about the clinical trial will be provided to individuals interested in participating, and all questions regarding the trial will be addressed. Those who remain interested will be referred to Peking Union Medical College Hospital for screening. The hospital will organize the informed consent process for screening (see Appendix 1-II, Part 1). Individuals who agree to undergo screening will be assigned a screening registration number, and their personal information will be collected. They will then undergo physical examinations, specimen collection, and laboratory testing. Volunteers who meet the inclusion criteria will be asked to provide informed consent for participation in the clinical trial (see Appendix 1-II, Part 2), and will be assigned a randomization number and enrollment number in preparation for entering the clinical trial. The flowchart for volunteer recruitment and screening is as follows:

[figure not shown]

**Figure 1 Subject recruitment and screening flowchart**

## 6.4 Phase Ib Protocol

This Phase Ib clinical trial requires 36 participants and will span 38 weeks. The primary objective is to observe the safety and tolerability of a combined immunization regimen consisting of three doses of 2 mg or 4 mg DNA vaccine followed by one dose of rTV vaccine in healthy volunteers who have or have not previously received the smallpox vaccine. Additionally, the trial will preliminarily assess the immunogenicity of this regimen.

Participants who have received the smallpox vaccine must meet at least two of the following conditions:

1. Age  $\geq 27$  years;
2. Presence of a typical smallpox vaccination scar on the upper arm;
3. Positive vaccinia antibody test result.

Participants who have not received the smallpox vaccine must meet all of the following conditions:

1. Age  $< 27$  years;
2. Absence of a typical smallpox vaccination scar on the upper arm;
3. Negative vaccinia antibody test result.

### 6.4.1 Inclusion and Exclusion Criteria of Study Subjects

|                           |
|---------------------------|
| Inclusion criteria |
|---------------------------|

1. Gender: No restrictions.
2. Age: 18 to 55 years old.
3. Follow-up and Specimen Collection: Able to attend follow-up visits and agree to venous blood sampling and specimen storage within 9 months after the first vaccination.
4. Informed Consent: Able to understand and agree to the content of the informed consent form.
5. Low Risk of HIV Infection:
  - No history of gonorrhea or syphilis.
  - No high-risk sexual partners (e.g., intravenous drug users, HIV-positive partners) in the past year.
  - No unprotected sex with non-regular sexual partners in the past year.
6. HIV and Syphilis Testing: Willing to undergo HIV and syphilis blood testing.
7. Contraception: Willing to use effective contraceptive measures with their partner from 2 weeks before the first vaccination until 6 months after the last vaccination. Female volunteers must agree to undergo urine pregnancy testing before each vaccination and during follow-up

visits.

### Exclusion criteria

#### 1. Psychological State:

- Individuals deemed psychologically unfit to participate in the trial by a psychologist.

#### 2. Pregnancy or Breastfeeding:

- Pregnant or breastfeeding women, or those planning to become pregnant during the trial.
- Close contacts (within 1 month after rTV vaccination) who are pregnant or breastfeeding.

#### 3. Medical History or Conditions:

- Congenital or acquired immunodeficiency diseases (e.g., AIDS) or close contacts (within 1 month after rTV vaccination) with such conditions.
- Ongoing treatments that may affect immune responses, such as:
  - Use of corticosteroids for more than 2 weeks.
  - Use of immunosuppressants (e.g., alkylating agents, antimetabolites).
  - Radiation therapy.
- Close contacts (within 1 month after rTV vaccination) undergoing such treatments.
- Immunosuppressive diseases (e.g., malignancies, organ or stem cell transplantation, agammaglobulinemia) or close contacts (within 1 month after rTV vaccination) with such conditions.
- History or current diagnosis of eczema or atopic dermatitis; current skin conditions causing skin damage (e.g., burns, chickenpox, impetigo, shingles, psoriasis) or close contacts (within 1 month after rTV vaccination) with such conditions.
- History or current diagnosis of hypertension, heart disease, diabetes, thyroid disorders, asthma, angioedema, asplenia, psychiatric disorders, psychological disorders, epilepsy, etc.
  - Conditions requiring repeated injections or blood sampling.
  - History of fainting or allergic reactions after vaccination.
  - Current acute infectious or febrile illnesses.

#### 4. Recent Medical Interventions or Behaviors:

- Received live attenuated vaccines within 2 months or other vaccines within 2 weeks.
- Received immunoglobulin or other blood products within 4 months.

- Participated in other medical product trials within 1 month.
- History of drug abuse, substance dependence, alcoholism, or heavy smoking.

#### 5. Abnormal Laboratory Results:

- HIV antibody positive or indeterminate, or HIV nucleic acid test positive.
- Anti-DNA antibody or anti-nuclear antibody positive.
- Hepatitis B surface antigen (HBsAg) or hepatitis C antibody positive, or rapid plasma reagin (RPR) test positive for syphilis.
- Immunoglobulin G, A, or M levels outside the normal range.
- Lymphocyte subset analysis showing abnormal levels of CD3+, CD4+, CD8+, CD8+DR+/CD8+, or CD8+CD38+/CD8+ cells.
- Hemoglobin levels  $\leq 110$  g/L for females or  $\leq 120$  g/L for males.
- White blood cell count  $\leq 3.3 \times 10^9$ /L or  $\geq 12.0 \times 10^9$ /L.
- Total lymphocyte count  $\leq 0.8 \times 10^9$ /L.
- Platelet count  $\leq 100 \times 10^9$ /L or  $\geq 400 \times 10^9$ /L.
- Abnormal biochemical indicators: alanine aminotransferase (ALT), aspartate aminotransferase (AST), creatine kinase (CK), CK-MB isoenzyme, cardiac troponin I (cTnI), fasting blood glucose, total bilirubin (TBIL), blood urea nitrogen (BUN), creatinine (Cr), etc., outside the normal reference range.
- Urine glucose  $\geq 15$  mmol/L or urine protein  $\geq 0.3$  g/L.

#### 6. Other Exclusions:

- Individuals unable to comply with the study protocol or provide informed consent due to medical, psychological, social, or occupational reasons.

These criteria ensure the safety of participants and the integrity of the trial results by excluding individuals at higher risk of adverse events or those whose conditions may interfere with the study outcomes.

### 6.4.2 Immunization and Follow-Up Plan

The Phase Ib clinical trial requires a total of 36 volunteers, including those who have and have not previously received the smallpox vaccine. These volunteers will be divided into three groups: a combined immunization group (24 individuals) receiving three doses of the DNA vaccine and one dose of the rTV vaccine, a DNA-only group (6 individuals) receiving three doses of the DNA vaccine alone, and a placebo group (6 individuals) receiving only a placebo. The combined immunization group is further divided into a low-dose and a high-dose subgroup, each consisting of 12 individuals. Recruitment will aim to include an equal number of individuals who have and have not received the smallpox vaccine in each

dose subgroup. Enrollment and vaccination will begin with the low-dose subgroup of the combined immunization group in the order of enrollment. The safety of the vaccine will be assessed within two weeks after each DNA vaccination in the low-dose subgroup. If no more than two vaccine-related adverse events of grade  $\geq 3$  (excluding fever above 39°C for no more than 3 days) occur, the trial will continue; if three or more such adverse events occur, subsequent vaccinations will be halted. Participants in both dose subgroups of the combined immunization group and the DNA-only group will receive three doses of 2 mg (low-dose subgroup) or 4 mg (high-dose subgroup) of the DNA vaccine at 4-week intervals. Enrollment and vaccination for the DNA-only group will commence simultaneously with the high-dose subgroup of the combined immunization group. If no more than two vaccine-related adverse events of grade  $\geq 3$  occur after each 4 mg DNA vaccination in the high-dose subgroup and the DNA-only group, the trial will continue; if three or more such adverse events occur, subsequent vaccinations in that dose subgroup will be stopped. If no more than two vaccine-related adverse events of grade  $\geq 3$  occur after the third DNA vaccination in each group, the combined immunization group will receive the rTV vaccine at the dose determined by the Phase Ia trial four weeks after the last DNA vaccination, while the DNA-only group will receive a placebo of the corresponding dose of the rTV vaccine. The placebo group will begin enrollment and vaccination at the same time as the low-dose subgroup of the combined immunization group and will receive placebos of the same volume as the DNA or rTV vaccines at the same time points. After the last vaccine or placebo administration, all participants will undergo at least six consecutive months of clinical and laboratory observation. In the Phase Ib trial, the interval between vaccinations in each group will be  $\geq 4$  weeks; if the time required for adverse reactions to heal or resolve exceeds 4 weeks, the interval between vaccinations will be  $\geq$  the actual time required for healing. The criteria for determining adverse events and their relationship to vaccination are detailed in Appendix 2 and Table 9.

Based on the data obtained from the Phase Ia clinical trial, which showed that the rTV vaccine was well tolerated at both 1 and 2 doses, with 2 doses being the highest safe dose determined in this phase, the Phase Ib clinical trial will use 2 doses as the vaccination dose for the rTV vaccine.

After immunization, participants will be observed for 24 hours, during which researchers will closely monitor local and systemic adverse reactions and complete raw data and CRF forms. Participants will then be given daily report cards and instructed on how to complete them. Participants must fill out the daily report cards every day for 2 weeks after DNA vaccination and for 4 weeks after rTV vaccination, and record any abnormalities that occur between follow-up visits on the daily report cards, which will be submitted to researchers at the next follow-up visit (Appendix 3). During the 2 weeks after DNA vaccination and the 4 weeks after rTV vaccination, participants must also complete a temperature chart for the respective periods. All adverse events occurring between follow-up visits will be recorded in the raw data forms, transcribed to the CRF forms, and entered into the database. Follow-up visits to the hospital will occur at weeks 1, 2, and 4 after DNA vaccination, and on days 3, weeks 1, 2, 4, 8, 12, 16, 20, and 24 after rTV vaccination. At each follow-up visit, researchers will record all participant-related data, including physical examinations and laboratory tests, in the raw

data forms and transcribe them to the CRF forms. During the trial, Phase Ib participants will need to visit Peking Union Medical College Hospital at least 20 times for trial-required visits, 14 of which will involve venous blood sampling. The immunization schedule, trial plan, and venous blood sampling plan for the Phase Ib trial are detailed in Tables 5, 6, and 7, respectively.

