### 6.5.8 Treatment of Adverse Events

When a participant experiences an adverse event during the clinical trial, the investigator at the clinical trial site must closely monitor the participant and provide appropriate treatment,

following these principles:

1. Immediate treatment for serious adverse events: Provide emergency care for serious adverse events (SAEs) without delay.

2. Discontinuation of immunization under the following circumstances:

- If the participant exhibits the following symptoms within 2 hours after vaccination:
  - Respiratory symptoms: including chest tightness, wheezing, palpitations, or difficulty breathing;
  - Circulatory failure symptoms: including pallor or cyanosis, bradycardia, weak or absent pulse, hypotension, hypothermia, or cold extremities;
  - Central nervous system symptoms: such as confusion, convulsions, or coma.
- If the participant experiences a grade 3 or higher systemic or local adverse event or laboratory abnormality related to vaccination.

3. Management of other adverse events: While conducting clinical observation and providing appropriate treatment, the timing of the participant's next vaccination should be postponed until the abnormal changes return to normal.

4. Handling adverse events after rTV vaccination: The assessment and management of adverse events following rTV vaccination should follow the principles for adverse reactions and management after smallpox vaccination (see Appendix 6).

In the event of a serious adverse event requiring emergency unblinding, the principal investigator of the clinical trial and the sponsor must jointly perform the unblinding.

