## 6.7.2 Early Termination of the Clinical Study

In the low-dose combined immunization group, if three or more vaccine-related adverse events of grade  $\geq 3$  (excluding fever above 39°C for no more than 3 days) occur after each vaccination, the sponsor and the clinical trial unit should terminate subsequent vaccinations for all groups. However, follow-up for the affected participants should continue at least until the adverse events are resolved.

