### I. General reactions after vaccination

#### (I) Typical local reactions after vaccination

After the successful smallpox vaccination, there are generally papules, blisters, pustules, crusting and scab falling off at the injection site, and also small lesions papules and blisters (called sub-pox) can be seen around the damaged skin, accompanied by localized itching and pain.

Typical local reactions after smallpox vaccination occur at the following time:

| Time After accination | Typical Vaccination Reaction                                                                                                         |
|-----------------------|--------------------------------------------------------------------------------------------------------------------------------------|
| Day 3-4               | A papule appears at the vaccination site.                                                                                            |
| Day 5-6               | The papule develops into a vesicle (blister) with a surrounding red halo, and the top of the vesicle becomes umbilicated (indented). |
| Day 8-9               | The vesicle turns into a pustule, reaching its maximum size between days 8 and 10.                                                   |
| Day 12+               | The pustule gradually dries and scabs begin to form.                                                                                 |
| Day 17-21             | The scab falls off, leaving a permanent scar.                                                                                        |

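### No group-level stopping rule counts vaccine-related grade 3 or higher events after rTV in the 4 mg + rTV arm; closing the gap is cheap, but the benefit is modest

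*Protocol*

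**What the plan says.** Protocol 6.4.2 and 6.7.2 hold four group-level count rules. All use the same threshold: up to two vaccine-related events of grade 3 or higher allow vaccination to go on, and three or more stop it.

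- **Low-dose combined group, 6.4.2.** Safety is assessed within two weeks of each DNA dose.
- **High-dose combined and DNA-only groups, 6.4.2.** The trial goes on if no more than two such events "occur after each 4 mg DNA vaccination in the high-dose subgroup and the DNA-only group, the trial will continue". Three or more stop later vaccinations in that dose subgroup.
- **Gate before rTV, 6.4.2.** If no more than two such events occur "after the third DNA vaccination in each group, the combined immunization group will receive the rTV vaccine".
- **Early termination, 6.7.2.** "In the low-dose combined immunization group, if three or more vaccine-related adverse events of grade" 3 or higher (short-lived fever above 39°C excluded) "occur after each vaccination, the sponsor and the clinical trial unit should terminate subsequent vaccinations for all groups".

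The rTV dose is common to both combined subgroups: "the Phase Ib clinical trial will use 2 doses as the vaccination dose for the rTV vaccine". Table 5 places it at week 12 in the low-dose arm and week 14 in the high-dose arm. Visits after rTV fall "on days 3, weeks 1, 2, 4, 8, 12, 16, 20, and 24 after rTV vaccination". Section 6.4.3 allows a second rTV administration four weeks after an unsuccessful one.

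**The concern.** The second primary objective in 6.1 is the safety and tolerability of three DNA doses, at 2 mg or at 4 mg, followed by rTV. The protocol has a count rule after rTV for the lower-dose combination and none for the higher-dose one, and gives no reason for the difference.

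Followed as written, a cluster of related grade 3 or higher events after rTV in the 4 mg arm obliges no one to hold rTV for arm members still waiting for it, or to hold a re-vaccination. The replicating vector is also the component for which Annex 6 lists a separate set of serious reactions.

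**Working it through.** **Coverage of the rules**

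| Rule | Group counted | After DNA | After rTV |
|---|---|---|---|
| 6.4.2, low dose | 2 mg + rTV | yes | no |
| 6.4.2, 4 mg | 4 mg + rTV and DNA-only | yes | no |
| 6.4.2, gate before rTV | each group | third dose | no |
| 6.7.2 | 2 mg + rTV only | yes | yes |

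The empty place is rTV in the 4 mg + rTV arm. Group sizes in 6.4.2 give 12 + 12 = 24 rTV recipients, so the uncovered arm is 12 of 24.

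**What the low-dose arm can show in advance.** From Table 5 the lead is 14 − 12 = 2 weeks. Annex 6 describes the typical pustule as "reaching its maximum size between days 8 and 10", so the main local reaction falls inside the lead. The low-dose visits at day 3, week 1 and week 2 after rTV fall at trial weeks 12.5, 13 and 14, so the first scheduled visit after the peak is in the week in which high-dose rTV is due. The lead covers half of the four-week diary period after rTV. It carries information on rTV itself, because the rTV dose is the same and 6.7.2 stops all groups. It carries none on an effect of 4 mg priming that 2 mg priming does not have.

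**Who could be spared.** rTV is the last scheduled dose, which leaves two sets of people:

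1. Arm members not yet given rTV. They can exist because vaccination follows the order of enrolment, because 6.4.2 lengthens the interval when a reaction takes more than four weeks to heal, and because under 6.5.8 a participant's "next vaccination should be postponed until the abnormal changes return to normal".
2. Four-week re-vaccinations. These should be few: the Synopsis reports that all 12 Phase Ia subjects had the expected local reaction and seroconverted.

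**Size of the benefit.** The protocol gives no event rate, so 5%, 10% and 20% are assumed. With at most one counted event per person and m persons already given rTV, all with known outcomes, the rule is met in time with probability

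P(X ≥ 3) = 1 − Σ(k = 0 to 2) C(m,k) p^k (1−p)^(m−k).

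For three undosed, m = 9. At p = 0.10 this is 1 − (0.387 + 0.387 + 0.172) = 0.053.

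| Undosed | m | p = 5% | p = 10% | p = 20% |
|---|---|---|---|---|
| 1 | 11 | 1.5% | 9.0% | 38.3% |
| 3 | 9 | 0.8% | 5.3% | 26.2% |
| 6 | 6 | 0.2% | 1.6% | 9.9% |

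These are upper bounds under the one-event assumption, since some earlier outcomes will not yet be known. The rules count events, not people, so multiple events per person would raise them. If events per person are Poisson with the same share of persons affected, the total has mean −m·ln(1−p), and the m = 9 row becomes 1.2%, 7.1% and 32.6%.

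With all 12 dosed, the same formula gives 2.0%, 11.1% and 44.2%. That is the chance of the rule being met at all; by then no first dose is left to spare.

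**What Phase Ia says about the rate.** There were 0 related grade 3 or higher events in 12 subjects. The one-sided 95% upper limit is 1 − 0.05^(1/12) = 22%. Those subjects had rTV alone, without DNA priming, so this does not settle the rate in the primed arm.

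**The case against.** The strongest reply is that the omission follows from what the rules do. They halt later vaccinations, the high-dose arm is the last cohort, and Table 5 puts its rTV in one nominal week. On that schedule a count after high-dose rTV has no scheduled dose left to stop. This stands, and it is why the benefit is modest. It does not remove the point, because the protocol itself allows postponed doses and re-vaccination.

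Other safeguards also stand. A related grade 3 or higher event ends that participant's immunization (6.5.8). SAEs go to the regulator within 24 hours, with copies to the sponsor and ethics committee, and grade 3 events go to the sponsor within 2 working days (6.5.7). Withdrawals due to adverse events are reported within 24 hours to the regulator, the sponsor and the IRB (6.7.1). The DSMB meets every two months (7.3.1). None of these sets a number of events at which the group's rTV must stop.

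Two stronger readings are tempting and not supported. A reader might take the 44% at a 20% rate as the protection lost; it counts all 12 as already dosed. A reader might also argue that rare complications outrun the two-week lead, such as encephalitis at days 9 to 15 in Annex 6. Section 2.2.1 gives Tian Tan encephalitis as 0.5 per million, so a three-event rule in 12 people is a poor instrument for it, and one case would already be an expedited SAE. Nothing in the protocol shows that 4 mg priming does change reactions to rTV; the point is only that the low-dose arm could not reveal it.

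**Conclusion.** The gap holds: no group-level rule counts related grade 3 or higher events after rTV in 12 of the 24 rTV recipients, in an arm whose safety is part of a primary objective. The document's wording establishes this without any assumption.

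The consequence is small to moderate and rests on assumed rates and on how many arm members are undosed when events appear, which the protocol does not fix. If all 12 receive rTV in the same week, only re-vaccinations can be stopped. A reader might infer that the 4 mg arm receives rTV without oversight; individual stopping, expedited reporting, the DSMB and the low-dose lead all contradict that. It is a cheap improvement that should be made, not a flaw that invalidates the design.

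**What to change.** Extend 6.7.2, and the matching sentence in 6.4.2, so that three or more vaccine-related events of grade 3 or higher after rTV in the high-dose combined group halt remaining rTV doses and re-vaccinations in that group pending safety review. Use the fever exclusion already in 6.7.2.

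The cost is one sentence in each section. No participants or visits are added. No further unblinding is needed, since 6.4.3 already unblinds clinical observers on the third day after rTV. The downside is a possible pause of the last rTV doses; its chance while first doses remain is bounded by the same table, under the same assumptions.

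Annex 2 appears to grade redness at the rTV site by two rows with different cut-offs. That affects what any such rule counts, but choosing between the rows is a clinical judgement. It should be raised separately and left out of this change.

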The grading of adverse events will be determined after review by the head of the clinical trial unit. The relationship between adverse events and vaccination will be preliminarily assessed by the researchers at the clinical trial unit, but the final determination will be made through discussion between the sponsor and the clinical trial unit and confirmed in writing.

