### 4. Inability to participate in follow-up or specimen collection:

- If a participant's repeated inability to attend follow-ups or provide specimens significantly impacts data collection, the sponsor and clinical trial unit may decide to terminate their participation early.

For participants who withdraw due to adverse events, the reason and date of termination must be recorded on the adverse event report form and reported within 24 hours to the Safety Supervision Department of the National Medical Products Administration (NMPA), the sponsor, and the Institutional Review Board (IRB). Whenever possible, follow-up should continue until the expected end of the trial, but at least until the adverse event stabilizes or resolves.

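### The limit of three related grade ≥3 events is counted per vaccination, and no cumulative participant count triggers a review before rTV is given

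*Protocol*

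**What the plan says.** Section 6.4.2 of the protocol describes "a low-dose and a high-dose subgroup, each consisting of 12 individuals", plus six DNA-only participants who also receive 4 mg, so 12 are vaccinated at 2 mg and 12 + 6 = 18 at 4 mg. The limit of three related grade ≥3 events appears in four places:

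- **2 mg, 6.4.2.** Safety is assessed within two weeks of each DNA vaccination. Brief fever above 39°C is excluded, and "if three or more such adverse events occur, subsequent vaccinations will be halted".
- **4 mg, 6.4.2.** If no more than two such events "occur after each 4 mg DNA vaccination in the high-dose subgroup and the DNA-only group, the trial will continue". This clause has no fever exclusion.
- **Release of rTV, 6.4.2.** The condition is no more than two events that "occur after the third DNA vaccination in each group, the combined immunization group will receive the rTV vaccine".
- **Early termination, 6.7.2.** For the low-dose group, it applies if three or more events "occur after each vaccination, the sponsor and the clinical trial unit should terminate subsequent vaccinations for all groups".

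Other provisions bear on what is known and who acts:

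- On relatedness, 6.5.6 states that "the final determination will be made through discussion between the sponsor and the clinical trial unit and confirmed in writing".
- Grade 3 events reach the sponsor within two working days (6.5.7).
- Vaccination of an individual stops under this condition (6.5.8, repeated in 6.7.1): "If the participant experiences a grade 3 or higher systemic or local adverse event or laboratory abnormality related to vaccination".
- For adverse-event withdrawals, the reason and date "must be recorded on the adverse event report form and reported within 24 hours" to the regulator, the sponsor and the IRB (6.7.1).
- The DSMB meets every two months and can recommend termination (7.3.1).

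**The concern.** The count starts afresh at each dose. With two reactors after dose 1, one after dose 2 and none after dose 3, three participants have had a related grade ≥3 event, yet every rule says continue. The same three events after a single dose would have stopped vaccination. Because reactors receive no further doses, fewer people are exposed at each step while the allowance stays at two, so the limit becomes looser relative to the number at risk.

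Those affected are the remaining participants, who go on to a replicating vector in the first human trial of the combined regimen. The protocol's own third safety question (Table 3) is cumulative: it counts participants with grade ≥3 events from first vaccination to 24 weeks after the last. No decision point before rTV uses that count.

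**Working it through.** The limit is stated without operating characteristics, so there is no figure of the plan's own to reproduce.

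**Step 1: what the rule alone allows.** At most two events per dose over three doses, one event per reactor, reactors removed:

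- 2 mg: 2 + 2 + 2 = 6 of 12 (50%), with 12, 10 and 8 people exposed at successive doses.
- 4 mg, both groups pooled as in the 4 mg clause: 6 of 18 (33%).
- 4 mg, if the wording of the rTV condition is read as a separate count for each group: 2 + 2 + (2 + 2) = 8 of 18 (44%).

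**Step 2: how often it could happen.** Inputs from 6.4.2: n = 12 or 18 (pooled), three DNA doses, continue at two events or fewer. Assumptions, since the protocol gives neither: the per-dose risk *p* of becoming a reactor, and the number of events per reactor. Participants are treated as independent.

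Let *k₁, k₂, k₃* be the new reactors after each dose and *a(k)* the probability that *k* reactors produce no more than two events. Then

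P = Σ Π_j [ C(m_j, k_j) p^{k_j} (1−p)^{m_j−k_j} a(k_j) ], with m_j = n − (reactors so far),

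summed over all patterns with k₁ + k₂ + k₃ ≥ 3.

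- One event each: a(0) = a(1) = a(2) = 1, otherwise 0.
- Half have two events: a(0) = 1, a(1) = 1, a(2) = 0.5² = 0.25, otherwise 0.
- One, two or three equally likely: a(0) = 1, a(1) = 2/3, a(2) = (1/3)² = 1/9, otherwise 0.

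Example, pattern 2/1/0 with n = 12, p = 5%, one event each: 0.0988 × 0.3151 × 0.6302 = 0.0196. All patterns with exactly 3, 4, 5 and 6 reactors give 0.1419 + 0.0398 + 0.0059 + 0.0004 = 0.188.

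Probability that the rTV condition is met although three or more have reacted:

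| n | Events per reactor | 1% | 2% | 5% | 10% | 15% |
|---|---|---|---|---|---|---|
| 12 | one | 0.4% | 2.6% | 18.8% | 42.0% | 38.3% |
| 12 | half have two | 0.2% | 1.1% | 7.0% | 12.8% | 9.3% |
| 12 | 1–3 equally likely | 0.05% | 0.3% | 2.0% | 3.5% | 2.4% |
| 18 | one | 1.3% | 7.1% | 33.5% | 35.2% | 14.3% |
| 18 | half have two | 0.6% | 2.8% | 11.1% | 8.4% | 2.4% |
| 18 | 1–3 equally likely | 0.2% | 0.8% | 3.1% | 2.2% | 0.6% |

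The figures fall when reactors have several events because the limit counts events: one participant with three events reaches it alone. Several events per reactor are plausible, since Annex 2 grades erythema, induration, swelling and other local signs separately.

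**Step 3: among trials that do reach rTV.** For n = 12, the share with three or more reactors at 5% and 10% risk is 20% and 56% (one event), 9% and 32% (half have two), and 4% and 18% (1–3 equally likely).

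**Step 4: when a cumulative count can add anything.** After dose 1 it equals the existing count. Before dose 3, with n = 12 and one event each, the probability of three or more reactors and no halt is 0.1, 0.8, 6.8, 21.4 and 26.9% across the five risks. So the decisions before dose 3 and before rTV are the two that matter.

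**The case against.** **The text may be cumulative already.** The low-dose sentence in 6.4.2 could be read that way, and the phrasing in 6.7.2 could describe when the count is checked rather than when it restarts. That leaves an ambiguity for the 2 mg group. It does not help at 4 mg or for the rTV condition, which looks only at events after the third dose.

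**Reviews exist.** A reader might infer that nobody sees the total or that no review takes place. The documents do not support that. Relatedness is settled in writing by sponsor and site, grade 3 events are reported promptly, and each adverse-event withdrawal goes to the regulator, the sponsor and the IRB within 24 hours. Low-dose safety is assessed after every DNA vaccination. First dose to rTV is 12 weeks at both dose levels (Table 5), so a two-monthly DSMB meeting would normally fall in between. What stands is narrower: that meeting may precede the later events, and none of these steps has a cumulative criterion or holds back rTV.

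**Those who receive rTV are non-reactors.** Correct: reactors stop individually, so it would be wrong to infer that they go on to rTV. Nor do the documents show that DNA reactions in some participants predict rTV harm in others. This argues for a review rather than an automatic halt.

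**The risk is probably low.** Sections 2.1.1 and 3 cite good tolerability of DNA vaccines, including doses of 3 mg and 5 mg. At 1–2% per dose the probabilities are small. That objection stands as to size.

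**Conclusion.** The point holds in limited form. As worded, the limit applies per vaccination at 4 mg, for the release of rTV, and in the low-dose termination rule. Three or more participants can have reacted before rTV without any limit being reached. What is missing is a review triggered by the cumulative count; knowledge of the events and oversight in general are provided for.

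The maxima of 6 of 12 and 6 of 18 follow from the rule alone, the latter on the pooled reading; three reactors are 25% of 12 but only 17% of 18. The frequency is not established by the protocol. With assumed per-dose risks of 1–2% it is about 0.05–3% (n=12) or 0.2–7% (n=18). A reader might take 19–42% (n=12) or 34–35% (n=18) as the expected size, but those figures need a risk of 5–10% together with one event per reactor, and nothing in the protocol supports either as likely. This is a worthwhile low-cost safety improvement, not a defect that makes the existing rule unusable.

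**What to change.** Keep the per-vaccination limit and add to 6.4.2 and 6.7.2:

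> Before DNA dose 3 and before rTV, also count the distinct participants with a related grade ≥3 event since first vaccination at that dose level (of 12 at 2 mg; of 18 at 4 mg, both 4 mg groups together), using the same event definition as the existing limit for that dose level (brief fever excluded at 2 mg only, unless the exclusion is also added to the 4 mg limit). If three or more, the next dose or rTV waits for a documented sponsor and DSMB review, ad hoc if needed.

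The count uses data already held. It requires no further unblinding: all 18 in the second phase receive the same 4 mg DNA, and the 2 mg count uses the group that the existing rule already counts.

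The cost is an occasional extra review or short delay, which the interval of four weeks or more allows. With one event per reactor, a review would be triggered at either decision in 0.4% (n=12) or 1.3% (n=18) of cases at 1% risk, 2.6% or 7.1% at 2%, and 43% or 40% at 10%, where a review would be wanted.
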